# Central venous stenosis after subclavian versus internal jugular dialysis catheter insertion (CITES) in adults in need of a temporary central dialysis catheter: study protocol for a two-arm, parallel-group, non-inferiority randomised controlled trial

**DOI:** 10.1186/s13063-023-07350-9

**Published:** 2023-05-12

**Keywords:** Central vein stenosis, Central venous stenosis, Subclavian vein, Internal jugular vein, Central dialysis catheter, Right supraclavicular fossa view, Randomised controlled trial

## Abstract

**Background:**

The right internal jugular vein is currently recommended for temporary central dialysis catheters (tCDC) based on results from previous studies showing a lower incidence of central vein stenosis compared to the subclavian vein. Data is however conflicting, and there are several advantages when the subclavian route is used for tCDCs. This prospective, controlled, randomised, non-inferiority study aims to compare the incidence of post-catheterisation central vein stenosis between the right subclavian and the right internal jugular routes.

**Methods:**

Adult patients needing a tCDC will be included from several hospitals and randomised to either subclavian or internal jugular vein catheterisation with a silicone tCDC. Inclusion continues until 50 patients in each group have undergone a follow-up CT venography. The primary outcome is the incidence of post-catheterisation central vein stenosis detected by a CT venography performed 1.5 to 3 months after removal of the tCDC. Secondary outcomes include between-group comparisons of (I) the patients’ experience of discomfort and pain, (II) any dysfunction of the tCDC during use, (III) catheterisation success rate and (IV) the number of mechanical complications. Furthermore, the ability to detect central vein stenosis by a focused ultrasound examination will be evaluated using the CT venography as golden standard.

**Discussion:**

The use of the subclavian route for tCDC placement has largely been abandoned due to older studies with various methodological issues. However, the subclavian route offers several advantages for the patient. This trial is designed to provide robust data on the incidence of central vein stenosis after silicone tCDC insertion in the era of ultrasound-guided catheterisations.

**Trial registration:**

Clinicaltrials.gov; NCT04871568. Prospectively registered on May 4, 2021.

**Supplementary Information:**

The online version contains supplementary material available at 10.1186/s13063-023-07350-9.

## Introduction

### Background and rationale {6a}

Despite a lower incidence of infectious and thrombotic complications with subclavian vein catheters [1], the right internal jugular vein is currently recommended for temporary central dialysis catheter (tCDC) placement as it results in fewer catheter misplacements (1.4% vs 9.1% for the right subclavian vein [2]) and a lower incidence of central vein stenosis (CVS; 10% vs 42% for the subclavian veins [3]). CVS causes significant morbidity (e.g. increased number of catheter-related infections and earlier catheter removal) in haemodialysis patients [4] and subclavian vein stenosis will generally preclude the use of the entire ipsilateral arm for venous access.

There has been conflicting data regarding CVS incidence when comparing the subclavian and internal jugular veins [5–7]. An important shortcoming of most studies is that vascular imaging was performed for clinical indications which could have introduced a bias because patients without CVS are then more likely to be underrepresented. Furthermore, the definition of CVS varies between studies. A CT venography is deemed as a good modality since it is easily performed, readily available and time efficient [8]. It allows for visualisation of venous anatomy, patency and the presence of collaterals. Ultrasound, which is readily available in almost all intensive care units and recommended to be used during central venous catheterisation to increase success rates and decrease the numbers of mechanical complications [9], could also be used for systematic screening of patients to assess central vein patency before choosing the access site. Detection of venous stenosis may prevent attempts at central venous catheterisation that would be unsuccessful or could exacerbate the patient’s symptoms.

In addition to the previously described advantages of less infectious and thrombotic complications, the subclavian route may be more comfortable for the patient during insertion and also later on. Secondly, given that the subclavian route is further away from moving body parts compared to the internal jugular and the femoral routes, patient movement is less likely to affect the dialysis blood flow. Thirdly, the internal jugular and femoral routes are sometimes unavailable for catheterisation (e.g. due to local infection, thrombosis or other catheters in situ).

The catheter fabrication material (polyurethane vs silicone) may also have an impact on CVS incidence [6]. Polyurethane catheters (which were commonly used in previous studies) are stiffer and less compliant with the venous vessels and may thus have a greater impact on the vessel walls compared to softer silicone catheters.

To summarise, the subclavian route offers several advantages when placing dialysis catheters, but it is rarely used due to previous studies (with some methodological concerns) that have demonstrated a higher incidence of CVS compared to internal jugular catheterisation [10]. In an attempt to challenge this axiom, we designed the proposed two-arm, parallel-group, non-inferiority randomised controlled trial using silicone catheters inserted in the right subclavian or the right internal jugular vein.

### Objectives {7}

#### Hypothesis

After insertion and use of a silicone tCDC for ≥ 7 days, the incidence of post-catheterisation CVS is non-inferior when the right subclavian route is used as compared to the right internal jugular route.

#### Objectives

To determine if the incidence of post-catheterisation CVS detected by a CT venography performed 1.5–3 months after removal of the tCDC is non-inferior when the right subclavian route is used as compared to the right internal jugular routeTo compare the performance of a focused ultrasound examination of the central veins to detect CVS with a CT venography (golden standard) with a threshold ofa50% venous diameter/area reduction (corresponding to moderate CVS in this study), as this is the commonly used definition of CVS [11]b80% venous diameter/area reduction (corresponding to severe CVS in this study), as it has been suggested that the severity of central veno-occlusive disease must reach a diameter reduction around 80% before upstream changes in blood flow are detectable by current Doppler techniques [12]To compare the patients’ experience of discomfort and pain between the groupsaDuring the catheterisation, using a questionnaire (Additional file 1) handed out immediately after insertionbWhen carrying the catheter, using a questionnaire (Additional file 2) handed out as soon as possible after catheter removalTo compare the function of the tCDC during dialysis or plasmapheresis between the groups, using a questionnaire filled out by the dialysis nurse after each treatment session. The questionnaire (Additional file 3) includes both objective and subjective parametersTo compare the catheterisation success rate (defined as catheter tip placement in the right atrium or in the superior vena cava with the catheter aligned with the vessel) between the two groups using a post-procedural chest x-rayTo compare the number of mechanical complications (defined as arterial puncture/catheterisation and pneumothorax) between the groups

### Trial design {8}

This is a two-arm parallel-group, randomised controlled trial investigating whether the insertion of a dialysis catheter in the subclavian vein is non-inferior compared to the internal jugular vein with regard to the incidence of central venous stenosis.

## Methods: participants, interventions, and outcomes

### Study setting {9}

Patients will be recruited from at least five Swedish hospitals: Skåne University Hospital (Lund and Malmö), the county hospitals of Helsingborg and Jönköping, and Sahlgrenska University Hospital (Gothenburg).

### Eligibility criteria {10}

All patients that fulfil the inclusion criteria and lack all the exclusion criteria will be included in the study.

### Inclusioncriteria

Adult (≥ 18 years)In need of a tCDC with an expected treatment time of at least 7 daysInformed consent

### Exclusioncriteria

Intravenous pacemaker or a PICC-line via right-sided central veins in situKnown CVSAV fistula in the right armHistory of central venous vascular interventions including stents, dilatations and more (but not previous central venous catheterisation)Central venous catheter in the right internal jugular vein or in the right subclavian vein in situEither the right jugular vein or the right subclavian vein unavailable for catheterisation due to, e.g. local skin infection or thrombosisKnown allergy to iodinated contrast agentsBMI > 35 kg/m^2^No study physician available for the catheterisation

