## Interventions

### Explanation for the choice of comparators {6b}

Previous studies that used stiffer polyurethane tCDCs and had different methodological issues have demonstrated higher incidence of CVS after subclavian catheterisation as compared to internal jugular catheterisation. As the subclavian route offers several advantages, the current study will investigate if the incidence of CVS after insertion of a soft silicone tCDC in the right-sided subclavian vein is non-inferior compared to the right internal jugular vein which, in clinical practice, is the vein most commonly used.

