### Outcomes {12}

The primary outcome is the incidence of post-catheterisation CVS, defined as venous diameter reduction > 50% anywhere from the estimated insertion site to the tip of the catheter, detected by a CT venography performed 1.5–3 months after removal of the tCDC.

The CT venography will be performed according to a protocol designed for this trial (Attachment 1) with the purpose to keep the amount of intravenous contrast and radiation as low as possible (with a limit of 100 kV the amount of intravenous contrast is reduced by 30% and less radiation is needed by repositioning the shoulders in an arm holder).

The secondary outcomes are:To compare the performance of a focused ultrasound examination of the central veins to detect CVS with a CT venography (golden standard) with a threshold ofa50% venous diameter reduction, as this is the commonly used definition of CVSb80% venous diameter reduction, as it has been suggested that the severity of central veno-occlusive disease must reach a diameter reduction around 80% before upstream changes in blood flow are detectable by current Doppler techniquesTo compare the patients’ experience of discomfort and pain between the groups both during the catheterisation and when carrying the catheter by means of a questionnaire (Additional files 1 and 2)To compare catheter blood flow during dialysis and reported catheter-related dialysis dysfunction between the groups. A questionnaire to address this will be filled out by the dialysis nurse after every treatment, including both objective and subjective measures (Additional file 3)To compare the catheterisation success rate (defined as catheter tip placement in the superior vena cava or in the right atrium) between the two groupsTo compare the number of mechanical complications (defined as arterial puncture/catheterisation and pneumothorax) between the groups

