### Sample size {14}

Sample size calculation for the primary outcome was performed using an online calculator (https://www.sealedenvelope.com/power/binary-noninferior/) based on results of a previous study [3] that demonstrated a CVS incidence of 10% after tCDC insertion in the internal jugular vein. The rate of stenosis events in historical data has ranged from 10% for the jugular vein to 42% for the subclavian vein. Given the perceived and shown advantages with subclavian lines (less infections/thrombosis, more comfortable for the patient during insertion and use), we chose a 15% noninferiority margin as this is less than half the absolute difference, is judged to be clinically acceptable and results in a reasonable sample size. Calculations revealed that 50 patients per group are needed to be 80% sure that the upper limit of a one-sided 95% confidence interval (or equivalently a 90% two-sided confidence interval) will exclude a difference in favour of the standard group. In order to have 100 patients perform the CT venography for the per-protocol analysis, at least 200 patients will probably have to be included in the trial. Important differences found between the treatment groups (in terms of how many that did not complete the protocol) will be reported.

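### Stenosis already present at enrolment counts as post-catheterisation stenosis in a segment that differs by arm, so the risk difference can be biased in either direction

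*Protocol article*

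**What the plan says.** All references are to the protocol article.

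- **Exclusion criteria.** Known CVS, a history of central venous interventions, a central catheter in place in either study vein, and either study vein being unavailable are exclusions. The item on earlier interventions carries the exception "but not previous central venous catheterisation", with no limit on the vein or the type of catheter.
- **Outcomes {12}.** An event is a diameter reduction above 50% "anywhere from the estimated insertion site to the tip of the catheter", seen on a CT venography 1.5 to 3 months after removal.
- **Baseline variables** (where the primary analysis is described). The outcome is binary at follow-up and compared as an unadjusted difference in proportions with a one-sided 95% limit.
- **Methods for additional analyses {20b}.** Baseline imbalance between the groups is examined and, if needed, a stratified test is run. Neither vein status nor earlier catheters are named.
- **Reasons to exit the trial.** Patients whose randomised vein cannot be catheterised, or whose catheter tip cannot be placed correctly, leave the trial.
- **Discussion.** Checking patency by ultrasound before the procedure is called prudent, but it is not described as an eligibility step or as a baseline value for the outcome.

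**The concern.** The outcome's name implies new stenosis caused by the study catheter, but a single follow-up CT shows whatever stenosis is present. A patient with an earlier catheter and a silent lesion is eligible, and that lesion is counted.

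In most trials randomisation would spread such old events evenly and they would only dilute the comparison. Here it does not, because the part of the venous tree that is scored depends on the arm. The jugular segment is scored only in jugular-arm patients and the subclavian segment only in subclavian-arm patients; the brachiocephalic vein and superior vena cava are common to both. Two groups perfectly balanced on catheter history can still give a biased difference. For the same reason, a check for imbalance between the groups cannot detect the problem.

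At stake is the non-inferiority conclusion. Old jugular lesions inflate the control rate and can hide a true subclavian excess. Old subclavian lesions inflate the experimental rate and can make a sound result fail.

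**Working it through.** **Inputs from Sample size {14}.** "50 patients per group are needed to be 80% sure that" the upper limit excludes the margin; one-sided 5% level. The control rate comes from a study that "demonstrated a CVS incidence of 10% after tCDC insertion in the internal jugular vein". On the margin: "we chose a 15% noninferiority margin". The same section gives 42% as the historical subclavian rate.

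**Reproducing the stated sample size.** With 10% in both arms, n = (1.645 + 0.842)² × 2 × 0.10 × 0.90 / 0.15² = 49.5, so 50 per arm, as stated. At n = 50 the standard error is √(2 × 0.09/50) = 0.060 and power is Φ(0.15/0.060 − 1.645) = 80.4%.

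**Adding old lesions.** Let qJ and qS be the prevalence of unnoticed old lesions confined to the jugular and subclavian segments. The protocol gives neither, so the values below are assumptions. Treating old and new lesions as independent:

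- observed jugular rate pJ = 1 − 0.90(1 − qJ)
- observed subclavian rate pS = 1 − (1 − s)(1 − qS), where s is the true new rate (25% at the margin, 10% at equality)
- P(declare non-inferiority) = Φ((0.15 − (pS − pJ))/SE − 1.645), n = 50 per arm

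Example at the margin with qJ = 2%: pJ = 1 − 0.90 × 0.98 = 11.8%, pS = 25%, difference 13.2 points, SE = √((0.118 × 0.882 + 0.25 × 0.75)/50) = 0.0764. Then Φ(0.018/0.0764 − 1.645) = 7.9%.

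| Assumed old lesions | False non-inferiority (true 25% v 10%) | Power (true 10% v 10%) |
|---|---|---|
| None | 5.0% | 80.4% |
| Jugular-only 2% | 7.9% | 85.4% |
| Jugular-only 5% | 14.1% | 90.9% |
| Subclavian-only 2% | 3.3% | 68.2% |
| Subclavian-only 5% | 1.6% | 48.4% |
| 5% in each vein, or 5% in the shared segment | 6.0% | 68.6% |

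Exact enumeration of the Wald interval gives similar values. For the none, jugular 2% and subclavian 2% rows it gives 5.8%, 8.9% and 3.8% at the margin, and 80.6%, 85.7% and 69.1% at equality.

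**Which way does it go?** At the margin the observed difference is 0.15 + 0.75 qS − 0.90 qJ, so the two effects cancel when qS = 1.2 qJ. At equality they cancel when qS = qJ. If earlier catheters left lesions at the protocol's historical rates (10% per jugular, 42% per subclavian catheter), cancellation needs earlier subclavian exposure of only 0.10/0.42 = 24% of earlier jugular exposure at equality, or 1.2 × 0.24 = 29% at the margin. With an assumed 30% of patients having had a right jugular catheter, earlier subclavian exposure of 0%, 3%, 8.6% or 10% gives false non-inferiority of 9.8%, 7.8%, 5.0% or 4.4%.

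**The case against.** **The direction looks obvious, but is not established.** A reader might infer that the bias favours non-inferiority, because the right jugular is the vein "which, in clinical practice, is the vein most commonly used" and of the subclavian route the protocol says "it is rarely used due to previous studies". Both statements are about dialysis catheters. The exception in the exclusion criteria covers any earlier central venous catheter, including ordinary lines and past PICCs, and no frequencies by vein are given. The protocol's own rate per subclavian catheter is about four times the jugular one, so modest earlier subclavian use cancels or reverses the effect. The protocol also criticises the studies behind those rates, so this argument does not settle the direction either.

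**Large error figures need strong assumptions.** Jugular-only prevalences of 5% or 8% with no subclavian lesions would give about 14% or 22% false non-inferiority. At 10% per catheter they require 50% or 80% of patients to have had a right jugular catheter, with every resulting lesion unknown, confined to the jugular segment beyond the insertion site, and still passable. Those figures should not be taken as a fair range.

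**Baseline vein status is not ignored altogether.** Known CVS, past interventions and unavailable veins are excluded for both veins alike, and failed placement leads to exit. This stands and reduces the effect. A lesion that is unknown and still admits a catheter passes all these filters.

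**Details may sit elsewhere.** The eCRF or an analysis plan, neither shown, may record earlier catheters. That is a fair reason not to call the item missing. It does not change the outcome and the unadjusted primary comparison as the protocol fixes them.

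**Conclusion.** The point holds as a bias of unknown sign. The protocol admits patients with earlier catheters, scores one follow-up CT over an arm-specific segment, and makes no use of a baseline measurement in the outcome. Old single-vein lesions are therefore charged to one arm only, and neither randomisation nor the planned imbalance check removes this. The difference moves towards non-inferiority if old jugular lesions sufficiently outnumber old subclavian ones, and away from it otherwise.

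At an assumed 2% prevalence in one vein, the nominal 5% error becomes about 8% or about 3%, and 80% power becomes about 85% or about 68%. At the historical rates, 2% corresponds to 0.02/0.10 = 20% of patients with an earlier right jugular catheter, or 0.02/0.42 = 4.8% with an earlier right subclavian one, before the exclusions take effect. These sizes rest on the assumed prevalences, independence of old and new lesions, and the normal approximation. The documents do not support a claim that the trial is tilted towards non-inferiority. The uncertainty about direction is itself a reason to collect the information.

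**What to change.** 1. Record earlier right jugular, right subclavian and right-arm PICC catheters from the chart for every patient, if the eCRF does not already do so. This can be done retrospectively for patients already enrolled.
2. Pre-specify a sensitivity analysis of the 15-point test in patients with no earlier right-sided central catheter. Catheter history is a pre-randomisation characteristic, so the restriction does not itself break the randomised comparison.
3. Have the blinded CT read score both the right jugular and the right subclavian segment in every patient, over a segment defined in advance for the vein without a study catheter. That vein then gives the background stenosis rate per vein and shows which way the bias runs.

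Stratifying or adjusting for earlier catheterisation is not a remedy: within the stratum of patients with earlier catheters the scored segment still differs by arm, so the bias stays.

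**Cost.** One chart item, a few lines of analysis text and a slightly longer read, with no extra imaging. The restricted analysis is smaller: if 30% of patients dropped out of it, 35 per arm would remain and power at 10% versus 10% would be Φ(0.15/√(0.18/35) − 1.645) = 67%. The background rate is also imprecise: zero lesions in 50 untouched veins still leaves an upper one-sided 95% limit of 1 − 0.05^(1/50) = 5.8%. Both analyses support the interpretation of the primary result and do not replace it.

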### Who will take informed consent? {26a}

Patients will be identified and recruited by the inserting physician or by study personnel after referral for tCDC insertion. Both verbal and written study information will be given. Potential participants will be given the opportunity to ask questions about the study. Signed informed consent will then be obtained by a delegated research nurse or by the inserting physician.

### Additional consent provisions for collection and use of participant data and biological specimens {26b}

No additional consents are required. This trial does not involve collecting biological specimens for storage.

## Interventions

### Explanation for the choice of comparators {6b}

Previous studies that used stiffer polyurethane tCDCs and had different methodological issues have demonstrated higher incidence of CVS after subclavian catheterisation as compared to internal jugular catheterisation. As the subclavian route offers several advantages, the current study will investigate if the incidence of CVS after insertion of a soft silicone tCDC in the right-sided subclavian vein is non-inferior compared to the right internal jugular vein which, in clinical practice, is the vein most commonly used.

### Intervention description {11a}

All CDC-inserting physicians employed at the participating departments who have performed at least 100 ultrasound-guided central vein catheterisations (whereof at least 10 in the subclavian vein using the in-plane needling technique) will be asked to participate in the study as enrolling and inserting physicians. All participating physicians will certify that they fulfil these criteria in a signed curriculum vitae. To promote standardisation of the insertion procedure, all enrolling physicians must participate in an educational session on subclavian and internal jugular vein tCDC insertion.

